## Abstract

**Background:**

Cognitive behavioral therapy (CBT) is an effective intervention to treat depressive disorders in youth. However, 50% of adolescents still have depressive symptoms after treatment, and 57% drop out during treatment. Online CBT interventions have proven to be effective in reducing depressive symptoms and seem promising as a treatment for depressed adolescents. However, combining online programs with face-to-face sessions seems necessary to increase their effectiveness and monitor for suicide risk.

**Objective:**

In this study, we examine the effectiveness and cost-effectiveness of a blended CBT treatment protocol, a mixture of online and face-to-face CBT, as a treatment for clinically depressed adolescents.

**Methods:**

A pragmatic quasi-experimental controlled trial will be conducted to study the effectiveness of a blended CBT treatment protocol, in which blended CBT is compared with face-to-face CBT (n=44) and treatment as usual (n=44); the latter two were collected in a previous randomized controlled trial. The same inclusion and exclusion criteria will be used: adolescents aged between 12 and 21 years, with a clinical diagnosis of a depressive disorder, and referred to one of the participating mental health institutions. Assessments will be conducted at the same time points: before the start of the intervention, during the intervention (after 5 and 10 weeks), postintervention, and at 6- and 12-month follow-ups.

**Results:**

The primary outcome is the presence of a depression diagnosis at 12-month follow-up. Several secondary outcomes will be measured, such as depressive symptoms, quality of life, and suicide risk. Costs and effects in both conditions will be compared to analyze cost-effectiveness. Further, moderating (age, gender, alcohol and drug use, parental depression, and other psychopathology) and mediating effects (negative automatic thoughts, cognitive emotion regulation, attributional style) will be analyzed. Also, treatment characteristics will be studied, such as characteristics of the therapists, treatment expectancy, and therapeutic alliance. Dropout rates and treatment characteristics will be measured to study the feasibility of blended CBT.

**Conclusions:**

This study will examine the effectiveness and cost-effectiveness of a blended CBT program in which depressed adolescents are treated in mental health care. Results of blended CBT will be compared with face-to-face CBT and treatment as usual, and implications for implementation will be reviewed.

**Trial Registration:**

Dutch Trial Register (NTR6759); http://www.trialregister.nl/trialreg/admin/rctview.asp?TC=6759

**International Registered Report Identifier (IRRID):**

DERR1-10.2196/13434 RR1-10.2196/12654

## Introduction

Depressive disorders are among the most prevalent mental health disorders in adolescents [1]. They have a substantial effect on well-being, a high burden of disease, and a high risk of recurrence and chronicity [1,2]. At the age of 18 years, more than 15% of adolescents have suffered from a major depressive disorder [3]. Depression shows high comorbidity with other mental health diagnoses and increased social problems, decreased academic performance, increased school dropouts, more substance abuse, and an increased risk of suicide attempts and suicide [1,2,4]. Therefore, it is crucial that depressive disorders are treated effectively at an early age. In this study, we will test the effectiveness and cost-effectiveness of a blended treatment protocol [5] that combines internet-based and face-to-face sessions in an integrated treatment protocol targeting depressive symptoms in clinically depressed adolescents.

Several meta-analyses have shown that cognitive behavioral therapy (CBT) is an effective intervention to treat adolescent depression [6,7]. However, the effect size of CBT was found to be moderate (Cohen’s *d*=0.53) [7], and 50% of the adolescents were not free of depressive symptoms after being treated [8]. A recent Dutch randomized controlled trial (RCT) showed that the D(o)epression protocol (face-to-face individual CBT) was equally effective as treatment as usual (TAU; for example, interpersonal therapy, family therapy, medication, mindfulness training, creative therapy, and running therapy) in reducing depressive symptoms, as assessed by the Children’s Depression Inventory 2, and depressive disorders, as assessed by the semistructured interview Kiddie Schedule for Affective Disorders and Schizophrenia (K-SADS) [9,10]. Despite this result, a significant number of adolescents were not free of depressive symptoms at posttreatment (24%), the effects were moderate, the dropout was high (57%), and it was hard to motivate patients to finish the treatment. Therefore, it is important to develop an attractive and more suitable treatment for adolescents who do not prefer to visit a mental health professional each week. Exploring possibilities to improve existing treatments in an innovative manner with recently developed technologies to reach out to patients may prove a fruitful strategy.

One way to improve the flexibility and attractiveness of treatment of depressed adolescents is to offer online CBT. Earlier research showed that online CBT and face-to-face CBT had, on average, similar effects in the treatment of depressive disorders in adults [11-14]. It is suggested that online interventions can increase treatment motivation and expectancies for some patients and might decrease resistance because they can be easily tailored to the adolescents’ needs and adjusted to their daily lives [15]. Another benefit is that online interventions seem more easily accessible for adolescents. Only 25% of the adolescents who suffer from depression receive treatment, so improving access to treatment is crucial [16]. Furthermore, adolescents appear to prefer to work autonomously on their treatment, which is typical for online interventions [15]. Online interventions increase independence and self-confidence of patients because patients can choose when and how often they work on the intervention. It also strengthens their competences [17] and can enhance social support by peers through online chat [18]. For these reasons, online CBT is a promising intervention.

However, when treating depression, face-to-face contact with therapists is strongly advised because the suicide risk has to be monitored. Therefore, treatment that is only offered online, such as online CBT, might not be sufficient for depressed adolescents. There are several therapist-supported options that can be combined with online treatment. Some treatment protocols offer online CBT combined with support or guidance by a therapist through encrypted email or online chat, called guided CBT. Several systematic reviews found that therapist guidance in guided or blended CBT increases the effectiveness of online interventions and is also associated with higher completion of the treatment [11,12,19]. The so-called blended treatment protocols could even be more appropriate or adequate for depressed adolescents. In blended treatments, the online protocol and face-to-face sessions are fully integrated into one treatment protocol. These blended treatment protocols might contain the optimal combination of flexibility and attractiveness for adolescents and possibilities to monitor progression and risk for therapists during the face-to-face sessions.

Health care costs of depression treatment could potentially be reduced by offering CBT in a blended form compared with face-to-face CBT or TAU because some face-to-face sessions with a therapist are replaced by an online program. Fewer face-to-face sessions per patient are needed; therefore, therapists can treat more patients, which in turn can decrease the duration of waiting lists [17]. Both improving access and reducing waiting lists might allow more patients to benefit from treatment and, eventually, societal costs may be reduced as well [20]. In sum, blended treatment, defined as a combination of online treatment and face-to-face sessions, might be the solution to optimize the effectiveness of CBT for depressive adolescents by increasing motivation and expectancy, decreasing resistance (and dropouts), and tailoring the treatment [15,17], which will likely lead to reduced costs [20]. However, the effectiveness has never been studied before in clinically depressed adolescents who are referred for treatment [21]. The treatment protocol D(o)epression Blended was specifically developed to treat depressive disorders in clinically referred adolescents [22].

This study will examine the effectiveness and cost-effectiveness of D(o)epression Blended compared with D(o)epression face-to-face and TAU in clinically depressed adolescents. The adolescents in the latter two conditions already participated in a previous study comparing CBT with TAU using an RCT design [9,10]. Blended CBT treatment is expected to be more effective than TAU. Additionally, we expect blended CBT to be equally effective as face-to-face CBT. We also will study the intervention effect of depression severity, quality of life, suicide risk, and comorbidity. The costs of the interventions in the three conditions will be compared to analyze the cost-effectiveness. In addition to examining the effectiveness and cost-effectiveness, we will examine who the intervention is effective for by testing several moderators (age, gender, ethnicity, family income, alcohol and drug use, life events, degree of conflicts, parental depression, and other psychopathology) and how the intervention works by studying several mediators (negative automatic thoughts, cognitive emotion regulation, attributional style). Furthermore, treatment characteristics will be studied; that is, characteristics of the therapists, treatment expectancy, previous treatments, treatment satisfaction, therapeutic alliance, cooperation with treatment, and dropout rates to see whether the feasibility of D(o)epression Blended differs from face-to-face CBT and TAU, and whether these factors are related to the implementation and execution of the treatment program.

## Methods

### Design

This study will use a pragmatic quasi-experimental controlled trial design with one condition to evaluate the effectiveness and cost-effectiveness of blended CBT. Data from a previously conducted RCT, in which face-to-face CBT was compared to TAU, will be used to compare the different treatments. Therefore, this can be seen as a third additional condition to the previously conducted RCT.

A new cohort will be measured and treated in this study. The assessments and instruments will be identical to the previous study comparing CBT to TAU. Assessments will be conducted at baseline (T0), during the intervention after 5 weeks (T1), during the intervention after 10 weeks (T2), at 1 to 4 weeks postintervention (T3), at 6 months follow-up (T4), and at 12 months follow-up (T5). The overall study design is shown in Figure 1.

For the adolescents, it will take an estimated 60 minutes for T0; 40 minutes for T3, T4, and T5; and 30 minutes for T1 and T2. For parents, the measurements will take an estimated 45 minutes for T0, T3, T4, and T5, and an estimated 5 minutes for T1 and T2. For the therapist, T0 will take 3 minutes, and T1, T2, and T3 will take 1 minute to complete. Time estimations are based on earlier studies [10].

The study was approved by the medical ethics committee of the University Medical Centre Utrecht in the Netherlands (NL61804.041.17). Details are described according to the SPIRIT (Standard Protocol Items: Recommendations for Interventional Trials) guidelines [23]. The study was registered prospectively in the Dutch Trial Register (NTR6759) on October 16, 2017.

**Figure 1 figure1:**
[figure not shown]
Overall study design. T0=baseline; T1=during the intervention after 5 weeks; T2=during the intervention after 10 weeks; T3=at 1 to 4 weeks postintervention; T4=at 6 months follow-up; T5=at 12 months follow-up.

### Participants’ Eligibility

In total, 70 clinically depressed adolescents referred for treatment in one of nine participating mental health institutions will be asked to participate in this study, together with one of their parents. If the adolescent is 16 years or older, parents will only be approached with the adolescent’s permission. Inclusion criteria for the adolescents are (1) having a clinical diagnosis of a depressive disorder, (2) aged between 12 and 21 years, and (3) referred to one of the participating mental health institutions. Exclusion criteria are (1) acute risk of suicide, (2) drug abuse (as primary diagnosis), (3) pervasive developmental disorder (as primary diagnosis), (4) bipolar disorder (as primary diagnosis), (5) day care or admission to the clinical setting, and (6) insufficient knowledge of the Dutch language. If participants use medication, the dosage will be kept constant during the intervention.

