**Primary outcome**											
	Depression diagnosis	Kiddie Schedule for Affective Disorders and Schizophrenia	x	x		x			x	x	x

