### Primary Outcome Measure

Presence of the diagnosis of depression will be measured by the Present and Lifetime version of KSADS (K-SADS-PL) [26,27]. This widely used semistructured diagnostic interview assesses a wide range of diagnoses (present and lifetime), including their severity, taking into account the view of the adolescent and the parent, and will be conducted by a trained independent research assistant. Concurrent validity of the K-SADS-PL is supported; interrater agreement is high (93%-100%), and test-retest reliability is excellent for present and lifetime diagnoses of major depression [26].

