#### Preliminary Analyses

Possible baseline differences in demographic and diagnostic characteristics between the three conditions—(1) D(o)epression Blended condition, (2) D(o)epression face-to-face condition, and (3) TAU condition (the latter two conditions from the RCT, which has already been conducted)—will be checked by means of ANOVA, MANOVA, and chi-square analyses. If these variables show differences between the conditions, they will be entered as covariates in all models and regression models to test the effectiveness of the intervention.

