#### Analysis of Primary Outcome

The primary outcome measure (ie, presence of depression diagnosis) is dichotomous and will be tested with logistic regression analyses comparing the percentage of depressive disorders in the D(o)epression Blended condition in this study to the percentage of depressive disorders in the D(o)epression face-to-face condition and the TAU condition from the previous RCT.

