#### Analysis of Secondary Outcomes

The intervention impact on the secondary outcomes (depression symptoms, depression severity, depression improvement, quality of life, suicide risk, comorbidity) will be evaluated using linear mixed modeling with the baseline level of the concerning variable as the covariate.

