## Results

### Overview

The primary outcome is the presence of a depression diagnosis at 12-month follow-up. Several secondary outcomes will be measured, such as depressive symptoms, quality of life, and suicide risk. Costs and effects in both conditions will be compared to analyze cost-effectiveness. Further, moderating (age, gender, alcohol and drug use, parental depression, and other psychopathology) and mediating (negative automatic thoughts, cognitive emotion regulation, attributional style) effects will be tested. Also, treatment characteristics will be studied, such as characteristics of the therapists, treatment expectancy, and therapeutic alliance. The dropout rate and treatment characteristics will be measured to study the feasibility of blended CBT.

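### Adjustment of the primary logistic model for baseline K-SADS status depends on a between-condition test that can miss a moderate imbalance in small, non-randomised arms

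*Protocol article*

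**What the plan says.** All references are to the Protocol article.

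- **Entry (Participants' Eligibility).** The first criterion is "having a clinical diagnosis of a depressive disorder". No instrument is named, and no section states that a K-SADS diagnosis at T0 is required.
- **Primary outcome (Primary Outcome Measure; Results, Overview).** Diagnosis is assessed with the K-SADS-PL by a trained independent research assistant, and "The primary outcome is the presence of a depression diagnosis at 12-month follow-up".
- **Data at baseline (Table 1).** K-SADS diagnosis and K-SADS severity are both collected at T0, T3, T4 and T5.
- **Primary model (Analysis of Primary Outcome).** The outcome "is dichotomous and will be tested with logistic regression analyses comparing the percentage of depressive disorders in the D(o)epression Blended condition" with the percentages in the two earlier conditions. This section names no baseline term.
- **Covariate rule (Preliminary Analyses).** "Possible baseline differences in demographic and diagnostic characteristics between the three conditions" are checked by ANOVA, MANOVA and chi-square. Variables that differ become covariates in all models of effectiveness.
- **Secondary outcomes (Analysis of Secondary Outcomes).** These use linear mixed models "with the baseline level of the concerning variable as the covariate", with no condition attached.

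**The concern.** Entry and endpoint rest on different assessments: a clinical diagnosis lets the patient in, and a structured interview decides the outcome. The two need not agree at T0. A patient who is K-SADS-negative at T0 and still negative at 12 months is counted as free of depression, although on that measure there was nothing to remit.

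In a randomised trial such patients would be spread over the arms by chance. Here the blended cohort is new and the two comparators come from an earlier trial. Strengths and Limitations accepts that participants, therapists and context may differ slightly, and that the institutions are the same or similar. If clinical diagnosis was applied a little more loosely in one period, the T0-negative share would differ and would shift the primary percentages. A higher share in the blended arm flatters blended CBT; a higher share in a comparator hides a benefit.

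The remedy is already in the data, because T0 K-SADS is collected. The primary model uses it only if a significance test says so, while every secondary outcome gets its baseline value automatically.

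**Working it through.** **1. Is there a stated figure to reproduce?** None bears on this point. The planned N of 70 does reproduce from d = 0.53, two-sided alpha 0.05 and 80% power: 56 per arm, and 56 / (1 − 0.20) = 70. The point leaves that figure untouched.

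**2. How often would the baseline check find an imbalance?** Inputs: 44 per comparator (Abstract, Methods) and 42 recruited to blended CBT (Results, Recruitment). The T0-negative shares are assumptions. The test is an uncorrected two-group chi-square at two-sided 0.05, with power summed over exact binomial probabilities.

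| T0-negative, blended v comparator | Chance of being flagged |
|---|---|
| 20% v 10% | about 25% |
| 15% v 5% | about 35% |
| 10% v 0% | about 62% |
| 30% v 10% | about 66% |
| 20% v 0% | about 98% |

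Normal approximation for the first row: pooled share = (42 × 0.20 + 44 × 0.10) / 86 = 0.149. SE under no difference = √[0.149 × 0.851 × (1/42 + 1/44)] = 0.0768. SE under the alternative = √(0.16/42 + 0.09/44) = 0.0765. Power = Φ[(0.10 − 1.96 × 0.0768) / 0.0765] = Φ(−0.66) = 0.25. With the planned 70 in the blended arm it is about 28%. A three-group test with 42, 44 and 44 patients gives about 26% for 20/10/10.

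**3. What would an unadjusted imbalance do?** Let q be the share K-SADS-negative at T0, r the 12-month diagnosis rate in T0-positives, and s the rate in T0-negatives. Then

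P(diagnosis at 12 months) = (1 − q) r + q s.

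With the same r and s in both arms there is no treatment effect, and any difference comes from q alone. The documents give none of the three, so r = 0.24 to 0.50 and s = 0 to 0.10 are assumed ranges. The 24% in the Introduction is the share with remaining depressive symptoms after treatment in the earlier trial. It is not a 12-month K-SADS rate and serves only as a low anchor.

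For q = 20% v 10%:
- r = 0.50, s = 0: 0.80 × 0.50 = 0.40 v 0.90 × 0.50 = 0.45. Difference 5.0 points, OR 0.81.
- r = 0.24, s = 0: 0.192 v 0.216. Difference 2.4 points, OR 0.86.
- r = 0.24, s = 0.10: 0.212 v 0.226. Difference 1.4 points, OR 0.92.

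A pooled two-proportion test with 56 blended completers (70 × 0.80) against 44 would then reject in 5.4% to 8.0% of trials instead of 5%. For q = 30% v 10% the spurious difference is 2.8 to 10.0 points and rejection 6.5% to 17.4%, but the check would flag that imbalance about two times in three.

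**4. Boundary case.** With equal shares, for example 10% in each arm, the spurious difference is zero and rejection stays at 5.0%.

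**The case against.** A reader might infer that the primary analysis has no baseline adjustment at all. The document does not support that: Preliminary Analyses covers diagnostic characteristics and carries any that differ into all models, which takes in the primary logistic regression. T0 K-SADS status is naturally read as one of them, although it is not named.

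A reader might also infer that everyone K-SADS-negative at T0 counts as a treatment success. That is not so, because the endpoint is status at 12 months and a T0-negative patient who is positive then counts as depressed.

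The other arguments on that side are fair as far as they go. No section says that K-SADS-negative patients were enrolled. The cost-effectiveness section speaks of full remission on the K-SADS-PL, which suggests that patients are thought to start with the diagnosis. How the clinical diagnosis is established may be in the full protocol, so silence on that is not held against the article. The criteria and instruments are the same in all conditions, which works against unequal shares. A gross imbalance such as 20% v 0% would almost certainly be flagged. Adding T0 diagnosis itself as a covariate can also fail: it is constant if all are positive, and gives separation if no T0-negative patient has the diagnosis at 12 months.

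These arguments limit the size of the problem and shape the remedy. They do not rescue the rule: in a non-randomised comparison, a significance test in arms of this size decides whether a plainly prognostic baseline value is controlled. The article states that rule itself, so it is not a detail left to an unseen analysis plan.

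**Conclusion.** The point holds in a limited form. Control for baseline K-SADS status or severity in the primary model is conditional on a test that would miss a moderate imbalance about three times in four (20% v 10%, 42 v 44 patients). Secondary outcomes are adjusted for baseline without condition.

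Bias needs an unequal share of patients who are K-SADS-negative at T0 and mostly stay so. The documents do not give that share, so the actual size is unknown and may be nil. Under the assumed rates, a 10-point imbalance (20% v 10%) gives about 1 to 5 points of spurious difference and only slight inflation of the false-positive rate. Larger distortions need larger imbalances, which the planned check would more often catch. The case for change rests on the non-randomised design and the low cost of the remedy, not on evidence that bias is present.

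**What to change.** In Analysis of Primary Outcome:

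1. Prespecify T0 K-SADS severity as a covariate in the primary logistic model, whatever the Preliminary Analyses test shows.
2. Add a sensitivity analysis restricted to patients who are K-SADS-positive at T0 in all three conditions.
3. Report the T0 K-SADS-positive share by condition.
4. Do not rely on T0 diagnosis as a covariate if it is constant or causes separation; the restricted analysis then does that job.

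The cost is one more covariate and one extra run on data already collected, with slightly fewer patients in the restricted analysis. If every patient proves K-SADS-positive at T0, the restricted analysis equals the main one and the concern about T0-negative patients is closed.
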